## 8.2 - Secondary endpoints

Secondary endpoints include evaluations of efficacy and drug distribution. Evaluations of efficacy will include assessing the six-month progression free survival and median progression free survival, as well as the radiographic response rate. Volume of distribution of infusate will be evaluated radiographically by post-infusion MRI. Six month progression free survival is defined as the proportion of patients with stable disease at 6 months from surgery. Progression free survival is defined as time between surgery and earliest sign of disease progression or death. Overall survival is defined as the time from surgery until death.

Radiographic and Clinical Response Criteria

8.2.1 - Neurological Examination Status (compared to baseline assessment)

| Better | Must be on stable or decreasing dosage of corticosteroids |
| --- | --- |
| Stable | Failure to qualify as better or worse |
| Worse | Includes patients requiring increasing steroid dosage to remain stable |

If a patient requires a higher dose of steroid to maintain a stable neurological status, the patient will be considered worse for the purpose of response determination.

Patients who are clinically worse but whose steroids have been decreased at the time of deterioration will be considered stable until reassessed again at the baseline steroid dosage.

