### 8.2.2 - Radiographic Assessment compared to baseline MRI for patients with measurable disease

| CR | Total disappearance of all tumor with the patient off or only on adrenal replacement maintenance corticosteroids |
| --- | --- |
| PR | ≥50% reduction in product of perpendicular diameters of contrast enhancement or mass with no new lesions with the patient being on stable or decreased corticosteroid dosage |
| STAB | Failure to qualify for CR, PR, or PROG |
| PROG | >25% increase in product of perpendicular diameter of contrast enhancement or appearance of new lesions |

CR – Complete Response

PR – Partial Response

STAB – Stable disease

PROG – Progression of disease

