# 9 - Statistical Considerations

A standard phase I study design utilizing dose escalation as defined in section 2.0 will be used. A maximum of 42 patients will be accrued. Descriptive statistics of response/efficacy and tolerance of treatments will be used. Only patients who received study drug will be considered for endpoint analysis. Patients that did not receive study treatment (catheter placement and convection enhance delivery of carboplatin) will be replaced at the current dose cohort.

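### Six-month PFS is defined as the proportion with stable disease, which leaves patients in complete or partial response out of the numerator and contradicts the PFS definition beside it

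*Protocol*

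**What the plan says.** Section 8.2 lists six-month PFS among the secondary efficacy measures and defines it as follows: "Six month progression free survival is defined as the proportion of patients with stable disease at 6 months from surgery". The sentence after it reads: "Progression free survival is defined as time between surgery and earliest sign of disease progression or death".

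Section 8.2.2 sets out four radiographic categories. Its key gives "STAB – Stable disease", and its table defines STAB as "Failure to qualify for CR, PR, or PROG". CR and PR have their own rows. The best-response tables in section 8.2.3 also give CR, PR and STAB separate columns.

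On the analysis population, section 9 says: "Only patients who received study drug will be considered for endpoint analysis". It describes the efficacy analysis as descriptive and gives no target rate, hypothesis or decision rule for six-month PFS.

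**The concern.** Stable disease is not loose language in this protocol. It is a defined term, and its definition excludes responders. If the six-month sentence is applied as it stands, a patient whose tumor has shrunk by half or disappeared is treated like one who has progressed or died. The measure would then fall when patients move from stable disease into response.

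It would also disagree with the protocol's other PFS result. Median PFS comes from the time-to-event definition, in which responders are event-free. The six-month proportion would not match that curve at six months, although both come from the same patients. Section 1.2 says the efficacy results are meant to support later trials, so a reader planning one could take the lower figure at face value.

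**Working it through.** There is no stated six-month PFS figure to reproduce. The check compares the definitions and then does simple proportion arithmetic.

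**Step 1: how each patient is classified.** Take a treated patient with no earlier progression and apply both sentences of section 8.2, using the categories of 8.2.2.

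| Status at six months | Counted as six-month progression-free (stable-disease sentence) | Event-free (PFS sentence) |
|---|---|---|
| CR: "Total disappearance of all tumor with the patient off or only on adrenal replacement maintenance corticosteroids" | No | Yes |
| PR: "≥50% reduction in product of perpendicular diameters of contrast enhancement or mass with no new lesions" (plus a corticosteroid condition) | No | Yes |
| STAB | Yes | Yes |
| PROG | No | No |
| Died | No | No |

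The two definitions differ in the CR and PR rows and nowhere else.

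**Step 2: the denominator.** Section 9 restricts endpoint analysis to patients who received study drug. A responder who was treated is therefore in the denominator. Nothing in the protocol removes responders from it or says that stable disease includes them.

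**Step 3: size.** Let N be the number treated, S the number in STAB at six months and k the number in CR or PR. Assume every patient's six-month status is known.

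- As written: S/N
- Consistent with the PFS sentence: (S + k)/N
- Difference: k/N, that is, 1/N per responder

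Section 9 gives the largest N: "A maximum of 42 patients will be accrued". At N = 42:

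- k = 0: no difference
- k = 1: 1/42 = 2.4 points
- k = 2: 2/42 = 4.8 points
- k = 4: 4/42 = 9.5 points

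With fewer than 42 treated, each responder costs more than 2.4 points.

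**Step 4: an illustration.** Suppose 6 of 42 patients are progression-free at six months and 2 of them are in PR (both numbers assumed). The consistent definition gives 6/42 = 14.3%. The definition as written gives 4/42 = 9.5%. The gap is 2/42 = 4.8 points.

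**The case against.** The best defence is that the authors meant not progressed. The name of the endpoint and the PFS sentence beside it both point that way, and the protocol never says that responders count as failures; that follows only from applying the defined term. This is probably the intention. It does not repair the text, because 8.2.2 gives stable disease an explicit meaning and an analyst following the protocol would leave responders out. Nor is this a detail left for the SAP to supply: the protocol states the rule, and a SAP that did otherwise would contradict it.

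The second defence concerns importance, and it stands. The primary endpoint is DLT and MTD (sections 1.1 and 8.1). No escalation, stopping or accrual decision depends on six-month PFS. The number of responders may also be small: CR and PR carry corticosteroid conditions in 8.2.2, and 8.2.4 requires confirmation about four weeks later.

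A reader might infer more than the documents support:

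- **That this is the lead efficacy endpoint.** Sections 1.2 and 8.2 name it first but do not rank the secondary measures.
- **That the result could not be compared with any other six-month PFS.** The PFS sentence in 8.2 is sound, and a conventional six-month figure can be computed from the same records. No data are lost.
- **That the loss can be predicted from a 25% baseline.** A 3-month median with an exponential curve gives 0.5^(6/3) = 25%, and a 10–40% share of responders would lower it to between 0.25 × 0.90 = 22.5% and 0.25 × 0.60 = 15%. But the 3-month median in section 2.3 is background from intravenous carboplatin studies and not a projection for this treatment. Neither the exponential form nor the responder share has any basis in the protocol.
- **That the figure could fall toward 0% because resection itself would register as response.** That needs a pre-resection baseline scan. Section 8.2.2 says only that comparison is with the baseline MRI. The eligibility text, which asks for stable steroids before that scan, suggests a preoperative one, but an MRI after catheter removal is also planned and 8.2.2 does not say which is the reference. This is a separate ambiguity and is not needed here.

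**Conclusion.** The inconsistency is real and can be verified from section 8.2 read with 8.2.2. As written, six-month PFS omits treated patients in CR or PR, contradicts the adjacent PFS definition, and is too low by k/N: 2.4 points per responder at N = 42, more per responder at smaller N, and zero if there are no responders.

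This rests on taking stable disease in 8.2 in the sense defined in 8.2.2 and on keeping all treated patients in the denominator, as section 9 indicates. The total effect depends on k, for which the protocol gives no expectation.

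Because the endpoint is secondary and descriptive and leaves the MTD untouched, this should be fixed before efficacy results are reported. It does not put the design in doubt.

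**What to change.** Replace the six-month sentence in section 8.2 with wording to this effect: six-month PFS is the proportion of treated patients who, six months after surgery, are alive and have not progressed (CR, PR or STAB), using the same progression and death events as the PFS definition in this section.

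The estimator and confidence interval can be left to the SAP. The SAP should allow for the scan timing: the study calendar in section 7 lists MRI at weeks 8, 16 and 30, with none at week 26. For a patient on that schedule, progression first seen on the week 30 scan would be dated after six months, so an estimate read off at 26 weeks would rest largely on week 16 imaging. The SAP should state how scans on either side of six months are assigned.

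The cost is one sentence in a small protocol amendment. No visit, procedure, dose or sample size changes.

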### 8.2.2 - Radiographic Assessment compared to baseline MRI for patients with measurable disease

| CR | Total disappearance of all tumor with the patient off or only on adrenal replacement maintenance corticosteroids |
| --- | --- |
| PR | ≥50% reduction in product of perpendicular diameters of contrast enhancement or mass with no new lesions with the patient being on stable or decreased corticosteroid dosage |
| STAB | Failure to qualify for CR, PR, or PROG |
| PROG | >25% increase in product of perpendicular diameter of contrast enhancement or appearance of new lesions |

CR – Complete Response

PR – Partial Response

STAB – Stable disease

PROG – Progression of disease

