# 4 - Patient Eligibility Criteria

4.1 - Population:

Patients, aged 18 to 70, with grade III or IV astrocytoma (anaplastic astrocytoma or glioblastoma), or grade III oligodendroglioma or oligastrocytoma (anaplastic oligodendroglioma or anaplastic oligoastrocytoma) at first or second recurrence are eligible to enroll in this protocol. Subjects are required to have radiographic confirmation of disease progression and a Karnofsky Performance Status of at least 60. Eligible patients must be at least 6 weeks out from last dose of nitrosoureas, bevacizumab and other antiangiogenic therapies, 8 weeks out from completion of radiotherapy (fractionated or stereotactic), and 4 weeks out from last dose of other cytotoxic chemotherapies. Patients cannot be receiving other investigational agents and must be on a stable dose of dexamethasone for ≥1 week prior to baseline MRI. The tumor progression must be amenable to craniotomy for resection. Candidates for the study include only those patients for whom craniotomy for tumor resection is recommended as treatment for their tumor progression.

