## 4.2 - Inclusion Criteria

- All patients must have progressive disease for which craniotomy and tumor resection is recommended as treatment.
- All patients must sign a consent form indicating that they are aware of the investigational nature of the study. The informed consent form will indicate that the patient has been made aware of all other appropriate therapies.
- Patients with histologically confirmed grade III or IV astrocytoma, oligoastrocytoma, and oligodendroglioma who are at first or second recurrence
- All patients require an initial diagnosis of a malignant glioma as outlined in the inclusion criteria which must be confirmed at the treating facility.
- Patients must have unequivocal evidence of tumor progression by MRI performed no longer than 28 days prior to study registration.
- Patients must have pathologically confirmed recurrence at the time of catheter placement.
- Patients must be on a stable or decreasing dexamethasone dosage for at least 1 week prior to baseline MRI.
- Patients must have been treated previously with radiation therapy and treatment must have been completed at least 8 weeks prior to surgery for catheter implantation
- Last dose of cytotoxic chemotherapy must have been at least 4 weeks (6 weeks for nitrosoureas) prior to catheter placement. Patients are eligible if they received bevacizumab or other anti-VEGF therapies, although the most recent dose must be at least 6 weeks prior to catheter placement.
- Patients previously treated with stereotactic radiosurgery, stereotactic radiotherapy, brachytherapy, Gliadel wafers or other intratumoral chemotherapy are eligible.
- Patients must have recovered from all prior therapy.
- Age ≥ 18 and ≤70 years of age
- Patients must have a life expectancy of ≥ 3 months and a Karnofsky performance status ≥ 60.
- Patients must have normal organ and marrow function as defined below:
  - leukocytes >3,000/mcL
  - absolute neutrophil count >1,500/mcL
  - platelets >100,000/mcL
  - hemoglobin >9 g/dL
  - serum calcium <12.0 mg/dL
  - total serum bilirubin < institutional ULN
  - AST(SGOT)/ALT(SGPT) ≤2.5 X institutional ULN
  - creatinine <1.5 X institutional ULN

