Patients, aged 18 to 70, with grade III or IV astrocytoma (anaplastic astrocytoma or glioblastoma), or grade III oligodendroglioma or oligastrocytoma (anaplastic oligodendroglioma or anaplastic oligoastrocytoma) at first or second recurrence are eligible to enroll in this protocol. Subjects are required to have radiographic confirmation of disease progression and a Karnofsky Performance Status of at least 60. Eligible patients must be at least 6 weeks out from last dose of nitrosoureas, bevacizumab and other antiangiogenic therapies, 8 weeks out from completion of radiotherapy (fractionated or stereotactic), and 4 weeks out from last dose of other cytotoxic chemotherapies. Patients cannot be receiving other investigational agents and must be on a stable dose of dexamethasone for ≥1 week prior to baseline MRI. The tumor progression must be amenable to craniotomy for resection. Candidates for the study include only those patients for whom craniotomy for tumor resection is recommended as treatment for their tumor progression.

5.4 - Outline of Treatment Plan – details below the outline

- Pre-operative assessment for enrollment in clinical trial (see above)
  - Tumor board confirms that the patient is an appropriate candidate for the clinical trial based on diagnosis and radiographic evidence of recurrent disease
    - Inclusion criteria met (see list above)
    - Exclusion criteria met (see list above)
  - The clinical trial is fully explained to the patient including all risks of the clinical trial and informed consent is obtained
- Surgery
  - Surgery occurs in the operating room at OSU Main Hospital
  - There are multiple objectives of surgery:
    - The tumor is surgically removed
    - Intraoperative frozen section confirms high grade glioma
    - Infusion catheters (2-4) are inserted into the brain around the tumor resection cavity
- Post-operative admission – hospitalization after surgery occurs in the OSU Main Hospital
  - patient is admitted to the ICU for the first 24 hours after surgery during which time the following occurs:
    - Monitoring for adverse events occurs continuously during hospitalization
    - vital signs and neurologic assessment hourly
    - CT to assess catheter placement
    - Labs as per study calendar (see below)
    - Neurologic assessment by neurosurgeon ([name]) and resident house staff daily
    - Neurologic monitoring by RN as per ICU standard of care

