## 5.10 - Inpatient care

All patients will be admitted to the neurosurgical intensive care unit (NICU) after surgery. They will receive standard postoperative care including hourly vital sign and neurologic assessment. Patients will be transferred from the NICU to the stepdown unit or ward based on their clinical status. They will remain in a monitored setting (ICU, stepdown unit or ward) for the duration of their infusion, receiving continuous vital sign monitoring and frequent medical and neurologic examinations. Once the catheters have been removed, they will receive standard postoperative care provided to patients who have had craniotomy for brain tumor resection.

The admitting neurosurgeon and house staff will be responsible for documenting daily neurologic and medical examinations and responding to any acute changes in neurologic or medical status. A separate NICU attending and house staff team will provide additional examinations while the patient is in the NICU. Daily blood tests will monitor for marrow suppression, electrolyte imbalances and liver dysfunction.

CT within the first 12 hours after surgery will verify catheter placement and assess for intracranial hemorrhage. MRI will be performed after catheter removal to assess for residual enhancement and, if possible, the volume of distribution of the infusate. While the patient is in the hospital, clinical evaluation will be performed per standard neurological-critical care guidelines. Baseline examinations prior to surgery and 24 hours after surgery will include full neurological and general examinations, mini-mental status examination and Karnofsky Performance Status.

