### 8.2.3 - Evaluation of Best Overall Response

The best overall response is the best response recorded from the start of the treatment until disease progression/recurrence (taking as reference for progressive disease the smallest measurements recorded since the treatment started). The patient's best response assignment will depend on the achievement of both measurement and confirmation criteria.

| Neuro  Status | MRI and/or CT status | | | |
| --- | --- | --- | --- | --- |
|  | CR | PR | STAB | PROG |
| Better | CR | PR | STAB | Unknown* |
| Same |  |  |  | PROG |
| Worse | Unknown* | | |  |

If objective response is unknown, than will reimage in 4 weeks and classify according to:

| Neuro  Status | MRI and/or CT status | | | |
| --- | --- | --- | --- | --- |
|  | CR | PR | STAB | PROG |
| Better | CR | PR | STAB | Unknown* |
| Same |  |  |  | PROG |
| Worse | Progression | | |  |

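### Section 8.2.2 rates response against a baseline MRI that precedes tumour resection, so surgery alone can meet the PR or CR tumour criterion, and its progression reference conflicts with 8.2.3

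*Protocol*

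**What the plan says.** **Reference for response.** Protocol 8.2.2 carries the heading "Radiographic Assessment compared to baseline MRI for patients with measurable disease" and defines CR, PR, STAB and PROG under it. CR is "Total disappearance of all tumor with the patient off or only on adrenal replacement maintenance corticosteroids". PR begins with "≥50% reduction in product of perpendicular diameters of contrast enhancement or mass with no new lesions" and adds a condition of stable or decreased corticosteroids. PROG is an increase of more than 25% in the product, or new lesions. Section 8 does not say when the baseline MRI is taken.

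**Where the term occurs elsewhere.** It appears only in eligibility text. The inclusion criteria (4.2) state "Patients must be on a stable or decreasing dexamethasone dosage for at least 1 week prior to baseline MRI". The population paragraph (4.1, repeated in 5.3) says patients "must be on a stable dose of dexamethasone for ≥1 week prior to baseline MRI". In the study calendar (section 7) the only MRI before treatment falls in the column for the 4 weeks before catheter placement. Follow-up MRIs are at weeks 8, 16 and 30.

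**What happens in between.** The first surgical objective in 5.4 is "The tumor is surgically removed". Catheters are placed at the same operation, and infusion follows.

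**A post-operative scan is already planned.** Section 5.10 says "MRI will be performed after catheter removal to assess for residual enhancement", and 5.4 gives residual tumour as its purpose. In the calendar it appears only as a footnote. No section makes it the reference for response.

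**Reference for progression.** Section 8.2.3, on best overall response, uses another rule: "taking as reference for progressive disease the smallest measurements recorded since the treatment started". Section 8.2 defines PFS from surgery to the earliest sign of progression or death and names no reference scan. It defines six-month PFS as the proportion with stable disease, a category defined only in 8.2.2.

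**The concern.** A response measured from a scan taken before resection adds the surgeon's work to the drug's effect. The trial has no control arm to separate the two. Section 1.2 offers the response rate and PFS as support for later efficacy trials, so a reader of the results would want to take them as information about carboplatin.

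Progression is a separate problem. Two adjoining sections give different denominators for the same 25% rule, and the PFS definition does not choose between them. Two assessors following the document could date the same patient's progression at different visits.

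**Working it through.** The protocol gives no extent of resection, growth rate or expected response rate, so there is no planned figure to reproduce. The check applies the protocol's own thresholds.

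**Notation.** r = post-operative product of diameters divided by the pre-operative product (assumed, 0.1 to 0.5). g = growth factor after surgery. d = doubling time of the product in weeks (assumed, 4 to 12), so g at week t is 2^(t/d), counting from surgery.

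**Thresholds from 8.2.2 and 8.2.3.**
- PR size criterion against the pre-operative scan: r × g ≤ 0.50.
- PROG against the pre-operative scan: r × g > 1.25.
- PROG against the scan after catheter removal, when that is the smallest measurement: g > 1.25.

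**Step 1: surgery alone.** With g = 1, any r ≤ 0.50 meets the PR size criterion, and r = 0 meets the tumour part of CR. Measured from the post-removal scan, g = 1 is no change for any residual, which is STAB.

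**Step 2: how much growth each reading allows.**

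| r | Growth still within PR size, 0.50/r | Growth before PROG under 8.2.2, 1.25/r | Growth before PROG from post-removal scan |
|---|---|---|---|
| 0.1 | 5.0-fold | 12.5-fold | 1.25-fold |
| 0.2 | 2.5-fold | 6.25-fold | 1.25-fold |
| 0.3 | 1.67-fold | 4.17-fold | 1.25-fold |
| 0.5 | 1.0-fold | 2.5-fold | 1.25-fold |

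**Step 3: would the response be confirmed?** Section 8.2.4 asks for a second assessment about 4 weeks after the first. With the first at the week-8 calendar MRI, confirmation falls near week 12. For r = 0.2:
- d = 12: week 8 is 0.2 × 2^(8/12) = 0.32; week 12 is 0.2 × 2 = 0.40. PR on size, and confirmed.
- d = 8: week 8 is 0.2 × 2 = 0.40; week 12 is 0.2 × 2^1.5 = 0.57. PR at week 8, not confirmed.
- d = 4: week 8 is 0.2 × 4 = 0.80. Never PR on this schedule.

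Confirmation at week 12 needs 2^(12/d) ≤ 0.50/r, that is d ≥ 12/log2(0.50/r). This gives d ≥ 5.2 weeks for r = 0.1, 9.1 weeks for r = 0.2 and 16.3 weeks for r = 0.3. In all these cases the tumour is growing throughout.

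**Step 4: progression for r = 0.2 and d = 12, no new lesions, steroids and neurology stable.**
- Under 8.2.2: week 26 is 0.2 × 2^(26/12) = 0.90, STAB; week 30 is 0.2 × 2^2.5 = 1.13, still STAB.
- From the post-removal scan: g at week 8 is 2^(8/12) = 1.59, an increase of 59%, PROG.

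**Step 5: delay if 8.2.2 governs.** The extra growth needed is 6.25/1.25 = 5-fold, or log2(5) = 2.32 doublings. That is 9.3, 18.6 and 27.9 weeks for d = 4, 8 and 12. In general the factor is 1/r, so the delay shrinks to one doubling time at r = 0.5.

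**The case against.** **The pre-operative baseline is inferred.** Section 8 does not date the scan. Section 5.10 uses the word baseline for examinations on both sides of surgery, and limiting the assessment to measurable disease makes most sense after resection. This has some force, because the intention may well have been post-operative. But the 5.10 examinations are neurological, general, MMSE and performance status, not imaging. Every use of the full term outside section 8 is an eligibility condition. Someone applying the text as it stands would use the pre-operative scan.

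**The response rate need not be high.** A reader might infer that nearly all patients would count as responders, since all are selected for resection. The documents do not support that. They give no extent of resection. PR also requires no new lesions and stable or decreased steroids, and CR requires the patient to be off steroids or on adrenal replacement only. A worse neurological status blocks either, and confirmation is required. Step 3 shows confirmation failing at an assumed 20% residual with 8-week doubling.

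**Progression is not necessarily hidden.** A reader might also infer that PFS is inflated across the board. Section 8.2.3 already refers progression to the smallest measurement since treatment began. Section 9 describes study treatment as catheter placement plus infusion, so the post-removal MRI can count. New lesions are PROG on either reading, and neurological worsening that persists at re-imaging is also progression. The 6.25-fold figure and the delays in Step 5 therefore hold only if 8.2.2 governs. What stands is the contradiction, together with a six-month PFS definition that leans on the 8.2.2 category.

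**The endpoints are secondary.** Section 9 plans only descriptive statistics for efficacy, and escalation depends on DLT alone. This stands and limits the weight of the point.

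**Conclusion.** The point holds and should be fixed. By the protocol's own usage, CR and PR in 8.2.2 are measured from a pre-resection scan, so a residual of 50% or less meets the PR size threshold without any drug effect. The radiographic response rate as defined cannot be read as drug activity. How many such responses would be recorded and confirmed cannot be determined from the documents, because it turns on the residual, the regrowth rate and the non-size conditions.

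For progression, the supported conclusion is narrower: 8.2.2 and 8.2.3 conflict, the PFS definition names neither, and six-month PFS borrows a term defined only in 8.2.2. Delay arises only under the 8.2.2 reading.

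The residual and doubling times are assumptions; the thresholds are the protocol's. The consequence is confined to secondary, descriptive endpoints: response rate, PFS and six-month PFS. The DLT and MTD endpoint and overall survival are unaffected.

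**What to change.** - In 8.2.2 and 8.2.3, name the MRI already planned after catheter removal as the reference scan, both for response and for deciding whether disease is measurable.
- Restrict the response-rate denominator to patients with measurable residual disease on that scan.
- Use one progression reference, the smallest product from that scan onward, in 8.2.2, in 8.2.3 and in the definitions of PFS and six-month PFS.
- Show the scan as an entry in the study calendar at the time the protocol already sets, after catheter removal, rather than only in a footnote.

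**Cost.** The change is to wording only; no scan is added. Fewer patients will be evaluable for response, and the response rate will probably look less favourable. The reference scan will carry some post-surgical enhancement, and its timing varies: infusion may start between postoperative day 1 and day 7 and lasts 72 hours, so the scan falls at the earliest about day 4 (1 + 3) to day 10 (7 + 3) after surgery. Enhancement that later fades could itself resemble a response, so the protocol should state how it is handled and record the date of the scan.

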## 5.5 - Pre-operative safety

All patients enrolled in the trial will have been discussed at the weekly neuro-oncology tumor boards and deemed appropriate for the study based on eligibility and exclusion criteria (see section 4). All enrolled patients must sign the surgical consent and study consent.

5.6 - Surgery:

Patients will undergo surgery, which includes tumor resection and catheter placement, in the operating room. On the day of tumor resection, up to 4 barium-impregnated catheters (Medtronic Becker EDMS Ventricular Catheter 20cm Barium Impregnated cerebrospinal fluid ventricular catheters; Medtronic, Inc., Minneapolis, MN or equivalent) will be placed stereotactically into gadolinium-enhancing areas and/or in areas of FLAIR/T2 abnormalities. Prior use of ventricular catheters for intracerebral convection enhanced delivery has been approved by the U.S. Food and Drug Administration (BB-IND-9184) and published in peer-reviewed literature[[31](#_ENREF_31)]. Catheters can be placed stereotactically into infiltrated tumor areas unlikely to be resected or catheters can be advanced from the tumor cavity into surrounding brain. If there is no histologic confirmation of a malignant glioma via frozen section during tumor resection, for example in a case where the recurrent lesion actually represents another histologic entity such as radiation necrosis, catheters will not be placed.

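### Section 8.2.2 lets a mass earn a response by shrinking but not count as progression by growing, so a clinically unchanged patient with a growing non-enhancing mass is scored stable and six-month PFS can be overstated

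*Protocol*

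**What the plan says.** The radiographic rules are in the table of Protocol section 8.2.2, which applies to patients with measurable disease.

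- Partial response (PR): "≥50% reduction in product of perpendicular diameters of contrast enhancement or mass with no new lesions", on stable or decreased corticosteroids.
- Progression (PROG): ">25% increase in product of perpendicular diameter of contrast enhancement or appearance of new lesions".
- Stable (STAB): "Failure to qualify for CR, PR, or PROG".

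Section 8.2 defines the endpoints that depend on these categories: "Six month progression free survival is defined as the proportion of patients with stable disease at 6 months from surgery", and "Progression free survival is defined as time between surgery and earliest sign of disease progression or death".

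Section 8.2.3 combines the MRI category with neurological status. A patient who is better or the same with a STAB scan is STAB overall. A patient who is worse with a STAB scan is unknown, is re-imaged at 4 weeks, and is called progression if still worse. Section 8.2.1 widens the meaning of worse: "If a patient requires a higher dose of steroid to maintain a stable neurological status, the patient will be considered worse".

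Non-enhancing disease is within the trial's scope. The MRI entry criterion in section 4.2 reads "Patients must have unequivocal evidence of tumor progression by MRI performed no longer than 28 days prior to study registration" and does not mention enhancement. Under section 5.6, catheters "will be placed stereotactically into gadolinium-enhancing areas and/or in areas of FLAIR/T2 abnormalities".

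**The concern.** The two rows of one table do not use the same measure. Mass is an alternative to contrast enhancement when disease shrinks, but not when it grows. Since STAB is the default, enlargement of an existing mass that does not enhance is radiographically stable whatever its size, provided no new lesion appears.

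For PFS the gap works in one direction: it can delay or miss an event but cannot create one. Six-month PFS is most exposed, because it is defined directly through stable disease. Section 1.2 says the efficacy results are meant to support later trials, so a rate that is too favourable could be carried forward as a benchmark.

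**Working it through.** The protocol states no PFS rate, power or event count that depends on this definition, so there is no figure to reproduce. The check applies the rules literally to test cases and then asks how far six-month PFS could move.

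**1. Test cases.** Lesion sizes are assumed. Blank cells in the 8.2.3 tables are read as merged with their neighbours.

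| Case | Change in mass product | MRI category, current text | MRI category with mass added to PROG |
|---|---|---|---|
| A. Mass 3 x 3 to 4 x 4 cm, enhancement unchanged | 16/9 - 1 = +77.8% | STAB | PROG |
| B. Mass 4 x 4 to 2.8 x 2.8 cm, enhancement unchanged | 7.84/16 - 1 = -51.0% | PR | PR |
| C. Enhancement product halves, mass 3 x 3 to 4 x 4 cm | +77.8% | PR | PROG |

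A and B show the asymmetry. C shows that the response rate is exposed as well, subject to the confirmation at about 4 weeks that section 8.2.4 requires.

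**2. Overall classification of case A under 8.2.3.**

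- Better or same: STAB, and it stays STAB.
- Worse, or needing more steroid to remain stable: unknown, then progression if still worse at the re-image.

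The gap is therefore confined to patients who are clinically better or the same. With mass added to PROG, a patient who is the same becomes PROG. A patient who is better becomes unknown, because 8.2.3 puts better with PROG in that cell.

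**3. Timing.** The section 7 calendar has follow-up MRI at weeks 8, 16 and 30. Six months is about week 26. Non-enhancing growth passed over at week 16 waits 30 - 16 = 14 weeks for the next calendar scan, which falls after the six-month mark. Clinical worsening, death or an extra scan could intervene.

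**4. Effect per patient.** Each patient counted as stable instead of progressed moves six-month PFS by 1/N.

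- N = 42 (the maximum in section 9): 1/42 = 2.4 points; 2/42 = 4.8; 4/42 = 9.5.
- N = 20 evaluable (assumed): 1/20 = 5.0 points.

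**5. A ceiling under stated assumptions.** Section 2.3 gives median PFS of about 3 months and median overall survival of about 9 months for intravenous carboplatin. Take both times as exponential.

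- Six-month PFS = 0.5^(6/3) = 0.25.
- Six-month survival = 0.5^(6/9) = 0.63.
- Progressed but alive at six months = 0.63 - 0.25 = 0.38.

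Let f be the fraction of progressions that show only as non-enhancing mass growth in a clinically unchanged patient. The documents give no value for f, so it is an assumption, taken as unrelated to death. Patients who have died are PFS events under section 8.2 in any case, so at most 0.38f can be wrongly counted as stable.

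| f (assumed) | Shift, 0.38f | Six-month PFS as read |
|---|---|---|
| 10% | 3.8 points | 28.8% |
| 20% | 7.6 points | 32.6% |
| 30% | 11.4 points | 36.4% |

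These are ceilings because some of these patients would show enhancement growth, a new lesion or worsening before six months.

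**The case against.** The strongest reply is that the text does not tie the PFS event to the PROG row. Section 8.2 runs PFS to the earliest sign of progression, so an assessor could count non-enhancing growth as an event. This stands for median PFS, which is delayed only if the assessor follows 8.2.2. It does not rescue six-month PFS, which is defined by stable disease. It also means that PFS and the 8.2.3 classification can disagree for the same patient.

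Second, the protocol has other routes to an event: neurological worsening, higher steroid need, new lesions and death. This also stands. A reader might infer that every growing non-enhancing tumour is scored stable. Sections 8.2.1 and 8.2.3 do not support that.

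Third, sections 5.8 and 5.11 say MRI will be evaluated by the McDonald criteria. The protocol does not set those out there, and section 8.2.2 writes its own rows, so naming the criteria does not reconcile them.

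Fourth, adding mass to PROG carries a risk of its own. Mass is undefined, every treated patient has had a resection and a 54 mL infusion, and section 5.8 itself anticipates imaging changes that suggest a treatment effect. Such change could be scored as progression. This stands and shapes the fix.

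Two further inferences are tempting. One is that the bias is largest in grade III tumours and distorts comparisons between histologies. Grade III tumours are eligible, but the protocol does not say that they enhance less, and it plans no such comparison. The other is to apply f to everyone who has had a PFS event by six months. That ignores the patients who have died, who cannot be scored stable.

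**Conclusion.** The point holds in limited form. Sections 8.2.2 and 8.2.3, read literally, classify a patient as STAB when an existing non-enhancing mass grows, no new lesion appears, neurological status is better or the same and steroids are not increased. If enhancement also halves, the MRI category is PR. This can overstate six-month PFS and the response rate, and can delay the events behind median PFS if 8.2.2 is followed. It is a stated rule that can give a wrong result, not a missing detail.

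The documents do not show that PFS will be overstated, or by how much. The number of patients affected cannot be derived from them. The firm figure is 1/N per patient, or 2.4 points at N = 42. The ceiling of about 0.38f rests on exponential times, on medians from intravenous carboplatin rather than resection plus convection enhanced delivery, and on an assumed f.

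Only descriptive secondary endpoints are affected. The DLT and MTD endpoint, the dose decisions and the sample size are untouched.

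**What to change.** Use the same measure in the PR and PROG rows of section 8.2.2. The preferred change is to make the PROG row read: more than 25% increase in the product of perpendicular diameters of contrast enhancement or mass, or appearance of new lesions.

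With it:

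- Define mass as measurable tumour, compared with a stated reference scan, and exclude change judged to be treatment-related. Say which reference applies: the heading of 8.2.2 points to the baseline MRI, while 8.2.3 takes the smallest measurement since treatment started as the reference for progression.
- State in section 8.2 that the PFS event and six-month PFS follow the 8.2.3 classification.

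Deleting mass from the PR row would also restore symmetry, but growth of a non-enhancing mass would still go uncounted.

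The cost is a short amendment. Mass is already assessed for PR, so no extra scan or visit is needed. Reported PFS may be slightly less favourable, and some treatment-related change could still be read as progression despite the exclusion.
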